**Nightly light exposure in pregnancy: blue-blocking glasses as an intervention to ease sleep disturbances and to improve mood**

This project will contribute with new knowledge on how nightly light exposure in pregnant women in their third trimester affect their sleep. Importantly, the project initiates new research on non-pharmacological treatment option of sleep disturbances by blocking the blue wavelengths of light in the evening and during nocturnal awakenings. Blue light is known to increase alertness through a recently described retinal receptor specialized for detecting daytime light signals. This project is highly innovative and may have significant practical implications

**Background**

Sleep disturbances are common in pregnancy (1-3), and the incidence increases during the third trimester. Poor sleep quality is reported in 39% of women in the early pregnancy, and in 54% during the third trimester (1). Up to 97% of pregnant women report nocturnal awakenings (4). For some, the sleep problems continue postpartum (2).

There are many conditions and sleep disorders that can cause disrupted sleep among pregnant women. Sleep apnea (breathing cessations during sleep), restless legs syndrome (an irresistible urge to move legs), and insomnia (difficulty in falling asleep and/or maintaining sleep) are common (5). Insomnia has been reported by so many as 62% of pregnant women, a number that is significantly higher than that found in the general population (10-15%) (6). The various hormonal and mechanical influences that contributes to fragmented sleep during pregnancy also reduce the time spent in the deep sleep (1). Disrupted sleep among pregnant women also include nocturia (a frequent need to get up and urinate at night), dyspnea (shortness of breath), nasal congestion, muscular aches and pelvic pains, fetal activity, leg cramps and also reflux (5).

Sleep is restorative for the brain, immune system, metabolic system, hormone regulation and many more physiological functions. Sleep disturbances are generally associated with a wide range of physical health problems, and impaired mental health (7). Insomnia typically co-occurs with several mental disorders, especially anxiety and depression. Cross-sectional and longitudinal studies have suggested that insomnia is a signiﬁcant risk factor for the development of depression (8, 9) and anxiety (10, 11). Depressive symptoms have been reported with 14.6% of pregnant women and were strongly associated with insomnia in the third trimester of pregnancy (6). Several studies have shown an association between sleep disturbances in pregnancy and adverse pregnancy outcomes for both mother and fetus, including preeclampsia, elevated serum glucose, depression, prolonged labor, cesarean birth, alteration in fetal growth and preterm birth (5, 12, 13). Also, long-term health outcomes such as hypertension, diabetes and obesity are demonstrated (12-14)*.*

Effective and safe treatments for sleep disturbances during pregnancy are current lacking. Medical treatments with medications such as benzodiazepines, hypnotic benzodiazepine receptor agonists, antidepressants, melatonin and antihistamines are available, however there is little research on the effects and potential side-effects, especially for the fetus, when used during pregnancy (15). Hence, medication is not a recommended first-line treatment (5). Non-pharmaceutical options, such as sleep hygiene counselling or cognitive behavior therapy are safe options, but evidence for a clinically effect on the pregnant population is scarce (5, 15). Another limitation is that treatments such as cognitive behavior therapy are time-consuming, costly, and often not readily available.

The nocturnal awakenings often involve the pregnant women to leave the bed and consequently light exposure. The electric light in the evening and during night increase alertness, disturb sleep, shift the timing of the circadian clock and impair the brains’ restorative slow waves during deep sleep (16). Sleep, alertness and circadian rhythms are biological processes that display endogenous, entrainable oscillations of about 24 hour. According to the phase response curve for light, exposure of light in the evening and night typically delays the circadian rhythm (17). Light also enhances alertness leading to a wakeful state (18). Hence, getting up several times a night during pregnancy may produce an imbalance between the internal biological timing, the sleep-wake schedule and quality and quantity of sleep.

**Blue blocking glasses as a safe intervention**

Recent studies have shown that use of blue-blocking glasses (BB-glasses) in the evening improve sleep quality (subjectively reported) among persons with insomnia, and prevent alertness caused by blue-light emitting screens such as smartphones and iPad (19, 20). The mechanisms behind involves specialized retina ganglion-cells (intrinsically photoresponsive Retinal Ganglion-Cells, IpRGC), responsible for detecting and conveying the circadian day light signal directly to the SCN. IpRGC respond to a narrow band of wavelengths, most sensitive to the frequencies between 446 and 484 nm; the blue light (21, 22). Amber/orange tinted glasses works as a filter by blocking wavelengths shorter than 530 nm and have been shown to preserve normal nocturnal melatonin levels in a light environment that otherwise completely suppresses the natural production of melatonin (23). “Virtual darkness” to the SCN is therefore achievable by blocking the blue wavelengths of light (24, 25). The use of BB-glasses in evening/night allows the melatonin-production to follow the natural cycle of light and darkness, even when electric light and light-sources such as smart-phones, iPad and TV are used. In a recent case study, we have demonstrated that sleep is rapidly transformed from very irregular to markedly regular during the use of BB-glasses (26). Importantly, blocking blue light during the evening and night is not reported to produce any harmful side-effects, and in contrast to medication it does not depend on detoxification processes in the liver. Treatment studies show that use of BB-glasses are effective in improving mood, as those wearing BB-glasses recovered more quickly for postpartum depression (19).

Women’s health in reproductive age is a deciding factor for the future population (27). Total sleep time and quality of sleep play an important role in both the mothers and the child’s health (5, 28). New knowledge about preventing sleep problems in pregnancy may avoid several of the aforementioned negative health outcomes (12, 13) Clinical trials of safe interventions for women with sleep disturbances during pregnancy are thus strongly warranted (5). The existing studies suggest that use of the BB-glasses may improve sleep quality by influencing the sleep physiology in different populations. Based on this, we want to examine the effects of BB-glasses to prevent ill-timed light exposure at night in healthy pregnant women during the third trimester from causing disturbed sleep. To our knowledge, this will be the first clinical trial using an optical filter as intervention for sleep problems in pregnant women, and the project has thus both high clinical and scientific importance.

**Aims**

The main aim of this project is to investigate the effect of BB-glasses used in the evening and night on Dim Light Melatonin Onset (DLMO), alertness (subjectively), sleep quality (subjectively and objectively), positive and negative affect and mood for pregnant women in the third trimester. Furthermore, we want to establish the prevalence of sleep disturbance, sleep-pattern and sleep-related behavior in the study population, and the association with daily/nightly light exposure.

The sub goals are:

1. To assess the light environment and sleep-pattern among pregnant women in the beginning of the third trimester.
2. To investigate the effect of blue-blocking glasses on sleep quality among pregnant women in the beginning of the third trimester.
3. To investigate the effect of blue-blocking glasses, in the evening and during the night, on DLMO, positive and negative affect and symptoms of anxiety and depression among pregnant women in the beginning of the third trimester.

**Hypotheses**

1) Exposure to light in evening and night among pregnant women are positively associated with evening and nocturnal alertness, delayed DLMO and inversely related to sleep quality.

2) Use of blue-blockers in the evening and night advances DLMO, facilitates sleep (subjectively and objectively) and decreases daytime sleepiness in pregnant women in the third trimester.

3) Use of blue-blockers in the evening and night lead to an increase in positive affect and decrease in negative affect, improved mental health as indicated by improved mood, reduced symptoms of depression and anxiety in pregnant women in the third trimester.

**Methods**

**Design**

[figure not shown]
This is a prospective longitudinal randomized controlled trial.

**Study population and procedure**

A sample of 60 pregnant women will, during the standard control about gestational week 24, be recruited through consulting midwifes at antenatal-healthcare centers in the Municipality of Bergen. We will recruit until 60 participants have completed the protocol.

The inclusion criteria are; 1) healthy nulliparous women, 2) expecting one child, 3) being in the third trimester of a normal pregnancy, 4) not working at night during the study protocol, 5) able to wear an actigraph during the daytime and nighttime.

Exclusion criteria are; fever and other health conditions affecting sleep.

All participants will be given information about the study (oral and written form) by the consulting midwife. If the pregnant women consent to participate in the study, further information is provided by the research team. To exclude women with serious eye-condition affecting the translucency of the eyes, the red reflex of both eyes will be checked. The pregnant women will start going through the study protocol at gestational week 28. For baseline data, the participants will be assessed with subjective and objective measures for 7 days followed by 14 days of the BB-intervention/control-intervention. See Table 1. Consenting participants will be randomized (by www.randomizer.org) to either intervention/control condition.

Figure 1 Flow diagram of recruiting and data collection progress

|  | **Week 1 Day 1** | **Day 2–6** | **Day 7** |
| --- | --- | --- | --- |
| Morning  During the day  Evening | Actigraphy/light recorder  Sleep diary, incl. items about restless legs (RLS) , alcohol and physical activity  Demography  The Relationship Satisfaction Scale (RS)  Bergen Insomnia Scale (BIS)  The Epworth Sleepiness Scale (ESS)  The Beck Anxiety Inventory (BAI)  The Beck Depression Inventory (BDI-II)  Perceived Stress Scale (PSS)  The Penn State Questionnaire (PSWQ)  Karolinska Sleepiness Scale (KSS)  Positive and Negative Affect Schedule (PANAS)  Preesleep Arousal Scale (PSAS) | Actigraphy/light recorder  Sleep diary  PANAS  KSS  PSAS | Actigraphy/light recorder  Sleep diary  PANAS  KSS  PSAS  Melatonin sample from saliva |
|  | **Week 2 Day 8** | **Day 9-14** |  |
| Morning  During the day  Evening | Actigraphy/light recorder  Sleep diary  ESS  (PSS)  (PSWQ)  PANAS  KSS  PSAS  *Randomization: BB-glasses/control-glasses* | Actigraphy/light recorder  Sleep diary  PANAS  KSS  PSAS  *BB-glasses/control-glasses* |  |
|  | **Week 3 Day 15** | **Day 16-20** | **Day 21** |
| Morning  During the day  Evening | Actigraphy/light recorder  Sleep diary  ESS  PANAS  KSS  PSAS  *BB-glasses/control-glasses* | Actigraphy/light recorder  Sleep diary  PANAS  KSS  PSAS  *BB-glasses/control-glasses* | Actigraphy/light recorder  Sleep diary  ESS  BIS  PANAS  KSS  PSAS  BAI  BDI-II  PSS  PSWQ  Melatonin sample from saliva  Ending intervention; *BB-glasses/control-glasses* |

Table 1 Instruments and procedures

**Intervention**

The intervention comprises blue-blocking glasses (orange-tinted), which remove more than 90% of the blue wavelengths; wavelengths shorter than 530 nm. (26) The control-glasses will be light grey, with no blue-blocking effect.

The intervention group and control group will be instructed to wear the BB-glasses/control glasses from two hours before normal bedtime at night, until they go to bed. They will be informed to not expose themselves for light without wearing the BB-glasses during the night, and if needed, like going to the bathroom during night, to wear the BB glasses.

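### The night-time wearing instruction covers both groups but names only the BB-glasses, which contradicts the control condition and, if followed, removes the night-time part of the contrast

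*Protocol*

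**What the plan says.** Two consecutive sentences in the Protocol, Intervention section, carry the wearing instructions.

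- Evening: "The intervention group and control group will be instructed to wear the BB-glasses/control glasses from two hours before normal bedtime at night", ending when they go to bed. Both groups are named, each with its own lens.
- Night: "They will be informed to not expose themselves for light without wearing the BB-glasses during the night". The subject is still both groups, but only the active lens appears. The same sentence then names it a second time, for women who have to get up: "if needed, like going to the bathroom during night, to wear the BB glasses".

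The paragraph before these defines the two lenses. The active one is orange-tinted and removes more than 90% of blue wavelengths; the control one is light grey and blocks no blue light.

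Elsewhere, Study population and procedure describes a baseline week "followed by 14 days of the BB-intervention/control-intervention", and Table 1 enters "BB-glasses/control-glasses" for the intervention days. Hypothesis 2 states "Use of blue-blockers in the evening and night advances DLMO", and Hypothesis 3 likewise concerns evening and night use.

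**The concern.** In a lens-against-lens trial, the wearing rule defines the treatment contrast. For the night, this rule gives the active lens to everyone, contrary to the definition of the control condition a few lines above.

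The night is not a side issue here. The opening summary presents the treatment as "blocking the blue wavelengths of light in the evening and during nocturnal awakenings". The Background says "Up to 97% of pregnant women report nocturnal awakenings", and adds that these awakenings often take women out of bed and into light. If control women are protected from blue light at night, by lens or by avoidance, the trial no longer tests that part of its rationale. The comparison becomes one of evening use only, reported as evening and night use.

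**Working it through.** The point is textual. No sample-size figure in the Protocol depends on it.

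**Step 1. Who is covered by the night sentence?** The sentence before it has the intervention group and the control group as its joint subject. The pronoun that opens the night sentence has no other antecedent.

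**Step 2. Does anything else set the night rule for controls?**

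| Place in the Protocol | What it gives | Settles the night for controls? |
|---|---|---|
| Intervention, evening sentence | Own lens for each group, until bed | No, stops at bedtime |
| Intervention, night sentence | Active lens only, both groups | Yes, but wrongly |
| Study population and procedure | Randomization to one of two conditions, 14 days | No, shows intent only |
| Table 1 | Both lens types on intervention days; rows for morning, day and evening | No, has no night row |
| Hypotheses 2 and 3 | Evening and night use | No, but they need a night contrast |

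**Step 3. What each reading does to the comparison.**

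| Reading | Night-time consequence |
|---|---|
| Assigned glasses (probable intent) | Contrast intact |
| Controls wear BB-glasses at night | Controls receive the active lens; night contrast lost |
| Controls hold no BB-glasses, so avoid all night light | Both arms have little blue light at night; night contrast lost |
| Sentence meant for the BB arm only (against the grammar) | Arms differ in a light-avoidance instruction as well as in lens; lens effect confounded, direction of bias unclear |

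Only the first reading is sound, and the text does not state it.

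**Step 4. Reach.** Table 1 places randomization on day 8 and the end of the intervention on day 21: 21 − 8 + 1 = 14 days. Assuming equal allocation (the ratio is not stated), 60 completers / 2 = 30 control women, and 30 × 14 = 420 control nights at most. The night after day 21 follows the last assessment, so the nights that can affect a listed outcome are 13 per woman, or 30 × 13 = 390. These are counts of nights, not an effect size. The 97% is a proportion of women reporting awakenings, not a nightly rate of light exposure.

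**Step 5. Illustration of dilution only.** The share of effect due to night wear is not given, so I assume a loss of 0% to 50%. The Protocol's minimum of 34 is reproduced with a repeated-measures interaction, f = d/2 = 0.25, two assessments, ρ = 0.50 and α = 0.05:

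λ = f² × N × 2 / (1 − ρ) = 0.0625 × 34 × 2 / 0.5 = 8.5, with df 1 and 32, giving power 0.807.

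At 60 completers on the same method:

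| Effect lost (assumed) | f | λ | Power |
|---|---|---|---|
| 0% | 0.25 | 15.0 | 0.97 |
| 10% | 0.225 | 12.15 | 0.93 |
| 25% | 0.1875 | 8.44 | 0.81 |
| 50% | 0.125 | 3.75 | 0.48 |

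This takes the Protocol's conversion of d to f at face value. If d = 0.5 is read instead as the group difference in change, the change SD is √(2 × (1 − 0.5)) = 1 in units of the outcome SD. Power with 30 per arm is then 0.48 with no loss, 0.30 with 25% lost and 0.16 with 50% lost. Neither set measures the actual bias.

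**The case against.** The best reply is that this is an editorial slip which nobody would act on. The preceding sentence pairs the two lenses, the control lens is defined as non-blocking, randomization is to one condition per woman, and Table 1 repeats the pair throughout. Nothing says that control women are given BB-glasses, so the version in which they wear the active lens needs equipment the Protocol does not provide for. Whether the wording reached any participant is unknown, because the participant instructions are not part of what I have seen.

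It can also be said that the outcomes are not equally exposed. KSS and PANAS are completed just before lights-off, and the final saliva sampling for DLMO is on the evening of day 21, so the intact evening contrast acts on these directly. Earlier nights may carry over, by an unknown amount. Measures of sleep maintenance, such as number of awakenings and wake time after sleep onset, are more exposed.

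Most of this stands. The slip is the likeliest explanation, the harm is conditional on staff or participants following the text, and any bias would vary by outcome. But the indications of intent do not supply a night rule. The only sentence that does is wrong, and control women without BB-glasses could still follow it by avoiding light at night.

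**Conclusion.** The concern holds. The Protocol's only night-time instruction contradicts its own control condition. If it is followed literally by both groups, the night-time part of the contrast disappears, the evening part remains, and the estimated effect of evening and night use is biased towards zero. The wording error is certain from the text. That bias would follow is conditional on the instruction being given as written, and its size cannot be derived from the Protocol. The reach is bounded at 420 control nights under equal allocation, of which 390 precede the final assessments. The conclusion does not depend on that count or on the power illustration. This is an error to correct before participants are instructed; it does not undermine the design.

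**What to change.** In the night sentence of the Intervention section, replace both mentions of the BB-glasses with *their assigned glasses (BB-glasses or control glasses)*. Both groups then receive the same rule about light at night, each with its own lens. Use the same wording in the oral and written instructions given to participants.

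The cost is two replacements in one sentence, repeated in the participant material. The hypotheses, sample size, schedule and equipment do not change.

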**Instruments/Measures**

*Actigraphy* (29). For indirect measure of sleep patterns, we will use a commercially available actigraph (Actiwatch Spectrum from Philips Respironics). This actigraph looks like a watch and is constructed to register motor activity. It is worn around the wrist and registers movements by a piezo-electric accelerometer. Motor activity for periods of thirty seconds will be recorded. Data can be converted to objective sleep parameters. Actigraphy has shown to be sufficiently sensitive to detect changes in sleep length (30).

*Light recorder* (29). The actigraph Actiwatch is also constructed to register light; total white light, blue, green and red light.

*Melatonin samples* from saliva for establishing DLMO on day 7 during baseline-week, and repeated the last evening of the consecutive intervention-week day 21.

*Sleep diary* (31). Daily subjective estimates of bedtime, rise-time, sleep latency, number of awakenings, wake time after sleep onset, final awakening time, rise time, total sleep time, sleep efficiency, sleep quality and daytime functioning.

*Pregnancy related complaints* during the night will be daily measured by self-reporting of itching of the skin, leg cramps, restless legs, pelvic pain, back pain, fetal movements, nausea, vomiting, reflux and nocturia. The response scale range from 1 (no complains) to 5 (extremely).

*Restless Legs* (RLS) (32) will be assessed using the diagnostic criteria from the International Classification of Sleep Disorders – third edition.

*Physical activity* (33) will be daily measured by asking “How many minutes were you physical active, which was enough to raise your breathing rate?” Participants will be asked to fill in the amount of minutes every day.

*Alcohol consumption* will be measured as daily subjective estimates by asking “Did you drink alcohol yesterday, and how many alcoholic drinks?” by responding 0 for no alcohol, or specify the number of alcoholic drinks.

*The Bergen Insomnia Scale (BIS)*(34). The BIS assesses symptoms of insomnia during the previous week, and are related to sleep onset, maintenance, early morning wakening insomnia, not feeling adequately rested, experiencing daytime impairment and being dissatisfied with current sleep. The response alternatives range from 0 (no days per week) to 7 (all days per week).

*Karolinska Sleepiness Scale* (KSS) (35)**.** Subjective sleepiness just prior to turning the lights off will be assessed with the KSS. KSS assesses subjective state sleepiness and consists of one item with a scale ranging from 1 (= being very alert) to 9 (= the highest level of sleepiness).

*Positive and Negative Affect Schedule (PANAS)* (36)***.*** Changes in positive and negative affect and emotions will be measured by this 20-item self-report schedule. This is a five-point response scale ranging from 1 (very slightly) to 5 (extremely). The participants will be asked to complete PANAS just prior to turning the lights off.

*Pre-Sleep Arousal Scale (PSAS)* (37) consists of 16 items and measures eight cognitive (e.g., intrusive thoughts) and eight somatic (e.g., sweating) manifestations of arousal during before sleep onset. This is a five-point response scale ranging from 1 (not at all) to 5 (extremely). Higher sum scores of the 16 items indicate higher state of arousal.

*The Epworth Sleepiness Scale* (ESS) (38) is a trait measure of daytime sleepiness. Respondents are instructed to rate off in eight different situations on a scale ranging from 0 (would never doze off) to 3 (a high risk of dozing).

*The Beck Anxiety Inventory (BAI)* (39) is a 21-items list of symptoms of anxiety for self-report questionnaire for measure the severity of anxiety. The instrument has a four-point response scale ranging from 0 (not at all) to 3 (Severely – it bothered me a lot). Higher sum scores of the 21 items indicate higher state of anxiety.

*The Beck Depression Inventory (BDI-II)* (40) consisting of 21 groups of statements measuring the experience of depression during the last week. This is a four-point scale, ranging from 0 (e.g. I do not feel sad) to 3 (e.g. I am so sad or unhappy that I can’t stand it). Higher sum scores of the 21 items indicate higher state of depression.

*The Penn State Worry Questionnaire (PSWQ)* (41) measures the trait of worry by 16 items. The response scale range from 1 (not typical) to 5 (very typical) and indicate the state of worry.

*Perceived Stress Scale (PSS)* (42). The PSS measures the degree to which situations in one's life are appraised as stressful. The instrument consist of 14 items, each scored on a five-point scale ranging from 0 (never) to 5 (very often).

*Relationship Satisfaction Scale (RSS)(43).* This instrument measures marital satisfaction and relationship quality. It consists of a 10-items list of statements related to satisfaction with the relationship, and has a 6-point scoring scale ranging from 1 (very agree) to 6 (strongly disagree). This measure is included in order to describe the characteristics of the study sample and as a control variable.

*Sociodemographic factors* will be measured by self-reports in order to describe the characteristics of the study sample. The participants will be asked about:

*Marital status;* by selecting one of the following categories: ‘married’, ‘cohabiting’; ‘single’ and ‘separated/divorced’.

*Level of education;* by indicating the completed level of education in 9 categories. The categories are divided on six groups based on number of in years of education. The responses will be scored from 1 (lowest education level) to 6 (highest education level).

*Income* by asking: ‘What is your and the baby’s father’s yearly gross income’? Participants will be asked to indicate the income of themselves and their partners in seven categories. The responses will be scored from 1 (lowest income) to 7 (highest income).

*Smoking* by 1 item ‘Do you smoke at present’? with 3 response options: not smoking, sometimes or daily.

*Age of the participant by* 1 item: ‘How many years are you?’. Participants will be asked to fill in number of years.

*Living conditions* by two items. ‘With whom do you live?’ (Spouse/partner, Parents, Parents-in-law, Children, No one, Other) and ‘How many people including you live in your home?’

